### 9.1.1 Sample Size Assumptions

In the initial design, we predefined grade II to IV acute GVHD as the primary endpoint. We hypothesized that non-inferiority of 7.5 mg/kg ATG against 10.0 mg/kg ATG was established if the difference of the 95% CI in grade II to IV acute GVHD between the two groups was within 15%. On the assumption of an incidence of grade II to IV acute GVHD of 30%, an estimated 197 patients in each group were required at the one-sided significance level of 5% with a power of 90%. After the analysis of the first 210 patients enrolled in the study, the 100-day incidence of grade II to IV acute GVHD was 28.9% and 27.8% in the 7.5 mg/kg and 10.0 mg/kg groups with a difference of 1.2% with 95% CI of -10.0% to 13.4%. The 1-year incidence of EBV DNAemia in the 7.5 mg/kg group was significantly lower than that in the 10.0 mg/kg group (27.1% in 7.5 mg/kg group vs 45.2% in the 10.0 mg/kg group). According to the recommendation of the data and safety monitoring committee, the change of the primary endpoint was made to evaluate the superiority of a dose level of 7.5 mg ATG on viral infections without increasing aGVHD after haplo-HSCT.

The sample size calculation is with the following assumptions:

1. Incidence of EBV DNAemia within 1 year post-transplantation in 7.5 mg group: 30%
2. Incidence of EBV DNAemia within 1 year post-transplantation in 10.0 mg group: 42%
3. a 1:1 randomization scheme
4. a 5% 1-tailed risk of erroneously claiming a difference in the presence of no true underlying difference by Chi-square test or Fisher’s exact test
5. a 80% chance of successfully declaring a difference in the presence of a true underlying difference (power)
6. 5% percent of cases drop

Under the above assumptions, a total sample size of 412 subjects is required (206 in each group).

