### 9.2.2 Analysis of safety

All the patients in the study will be included in the safety analysis. The safety end points included clinical symptoms and laboratory abnormalities, laboratory values and vital signs analyzed by means of the chi-square test.

All P values are based on two-sided hypothesis tests. Alpha is set at 0.05. SPSS 19.0 (SPSS Inc., Chicago, IL, USA) and R version 3.4.3 (R Development Core Team, Vienna, Austria) were used for all data analysis.

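### The sample size assumes a one-sided 5% test, but the analysis rule is two-sided 0.05; under that rule 412 patients give about 70% power, not 80%

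*Protocol*

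**What the plan says.** Section 9.1 describes a superiority comparison of 7.5 mg/kg against 10.0 mg/kg ATG on EBV DNAemia within 1 year. Section 9.1.1 assumes incidences of 30% and 42%, 1:1 allocation, 5% drop-out, "a 80% chance of successfully declaring a difference in the presence of a true underlying difference (power") and "a 5% 1-tailed risk of erroneously claiming a difference in the presence of no true underlying difference", with either a chi-square or a Fisher's exact test allowed. It concludes that "a total sample size of 412 subjects is required (206 in each group").

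Section 9.2.1, on efficacy, sets neither a significance level nor a sidedness. The only such rule in section 9.2 is at the end of section 9.2.2: "All P values are based on two-sided hypothesis tests", followed by "Alpha is set at 0.05". The sentence after it names the software for all data analysis.

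**The concern.** The size of the trial and the rule for reading its result rest on different type I error rates. A two-sided test at 0.05 that favours the lower dose works at a one-sided level of 2.5%, half the level used to derive 412. The power claim in section 9.1.1 therefore does not belong to the test that section 9.2.2 prescribes.

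The success criterion is also open. A result with a one-sided p between 0.025 and 0.05 would establish superiority under 9.1.1 and fail under 9.2.2, so the choice could be made after the data are seen. That matters more here than usual. The trial is open-label, and section 9.1.1 reports that the primary endpoint was changed after EBV incidence by arm had been seen in the first 210 patients (27.1% versus 45.2%). A criterion set in those circumstances has to be unambiguous.

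**Working it through.** **Inputs, all from section 9.1.1 except the last.** p₁ = 0.30 (7.5 mg/kg), p₂ = 0.42 (10.0 mg/kg), difference 0.12, mean p̄ = 0.36, power 80% (z = 0.8416), drop-out 5%, one-sided 5% (z = 1.6449). From section 9.2.2: two-sided 5% (z = 1.9600).

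**Step 1: reproduce 412.** With the unpooled normal approximation,

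n = (z_α + z_β)² × [p₁(1 − p₁) + p₂(1 − p₂)] / (p₂ − p₁)²

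- One-sided 5%: (1.6449 + 0.8416)² × (0.2100 + 0.2436) / 0.0144 = 194.8, so 195 per arm.
- Drop-out: 195 / 0.95 = 205.3, so 206 per arm and 412 in total. This matches the protocol exactly.

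The pooled-variance formula gives 196.8, so 197 per arm, or 208 per arm (416 in total) after drop-out. That is close but not identical.

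**Step 2: the same calculation at two-sided 5%.**

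| Formula | Evaluable per arm | Randomised per arm (÷ 0.95) | Total |
|---|---|---|---|
| Unpooled | 247.2, so 248 | 262 | 524 |
| Pooled | 249.98, so 250 | 264 | 528 |

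Neither is near 412. The stated size depends on the one-sided level.

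**Step 3: power of the planned size under each rule.** After 5% drop-out, 206 × 0.95 = 195.7, or about 196 evaluable per arm. With the usual approximation,

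power = Φ{ [ (p₂ − p₁)√n − z_α √(2p̄(1 − p̄)) ] / √(p₁(1 − p₁) + p₂(1 − p₂)) }

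- One-sided 5%: (1.680 − 1.6449 × 0.6788) / 0.6735 = 0.837, so power is 79.9%.
- Two-sided 5%: (1.680 − 1.9600 × 0.6788) / 0.6735 = 0.519, so power is 69.8%.

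Exact enumeration over the two binomial distributions agrees at 196 per arm:

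| Test | One-sided 5% | Two-sided 5% |
|---|---|---|
| Chi-square, uncorrected | 80.2% | 70.2% |
| Fisher's exact | 77.2% | 66.5% |

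If all 206 per arm are evaluable, two-sided power is 72.1% (chi-square) or 68.3% (Fisher).

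**Step 4: what can be detected with 80% power at two-sided 0.05.** With 196 per arm, 30% versus 43.6% and 28.5% versus 42% each give 80% chi-square power (80.3% and 80.3% exact). The detectable difference is therefore about 13.5 points rather than 12.

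**Step 5: the zone of disagreement.** At a mean incidence of 36%, the standard error under the null hypothesis is √(2 × 0.36 × 0.64 / 196) = 0.0485. The smallest significant observed difference is about 8.0 points under the one-sided rule (1.6449 × 0.0485) and about 9.5 points under the two-sided rule (1.9600 × 0.0485). If the design assumptions are true, the chance of a result that passes one rule and fails the other is 80.2% − 70.2%, or about 10%.

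**The case against.** The arithmetic in section 9.1.1 is sound: 412 and 80% both follow from its one-sided inputs. The one-tailed statement is specific to the EBV comparison, while the two-sided sentence is general and stands under a safety heading. A reader could therefore take the specific statement as governing the primary test, in which case the power is 80% as stated. Declaring the primary test one-sided at 5% in the analysis section would also remove the conflict. The two-sided rule is the stricter one, so following it does not inflate the type I error. At the interim incidences of 27.1% and 45.2%, two-sided power with 196 per arm would be about 96%, although those incidences prompted the endpoint change and may be optimistic. Finally, with about 59 or more expected events per arm, there is no small-sample reason to use Fisher's test.

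Part of this stands. The fault is a mismatch between two rules, not a miscalculation, and the 70% figure applies once section 9.2.2 governs. The Fisher figures matter only because section 9.1.1 leaves that test open.

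The heading does not settle the matter. The sentence covers all P values, the one after it covers all data analysis, and no other level or sidedness is given in section 9.2. If it were confined to safety, the analysis section would give no level for the primary test. A one-sided rule is possible in principle, but adopting the looser level now, after EBV results by arm have been seen, would be hard to defend.

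**Conclusion.** The point holds. The protocol gives two incompatible significance rules for its primary comparison, and the stated 80% power belongs only to the looser one. Under the rule in section 9.2.2, power for 30% versus 42% is about 70% with 196 evaluable per arm, and 72% with no drop-out. Restoring 80% at a 12-point difference would take about 524 to 528 randomised patients.

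These figures rest on the incidences and drop-out assumed in section 9.1.1 and on a chi-square comparison of simple proportions, the first of the two tests named there. The mismatch should be corrected before the primary result is read, because it affects both the power claim and the definition of success.

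**What to change.** State one level for the primary test, in the same terms in sections 9.1.1 and 9.2. The recommended choice is the two-sided 0.05 rule already in section 9.2.2 (equivalent to one-sided 0.025), moved or repeated where it plainly covers efficacy.

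Replace the error-rate and power statements in section 9.1.1 with wording such as: *With 412 patients randomised (196 evaluable per arm after 5% drop-out), the chi-square test at two-sided 0.05 has about 70% power for 30% versus 42%, and 80% power for a difference of about 13.5 percentage points.*

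Name the chi-square test alone as the powered test. Say also how it relates to the competing-risks cumulative incidence that section 9.2.1 prescribes for viral infections, so that the primary test is identified without doubt.

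The cost is wording only. No patients are added and the design does not change; the stated power falls from 80% to about 70%. If the sponsor prefers a one-sided 5% test, 412 and 80% can stay, but section 9.2.2 must then exempt the primary test explicitly and the protocol must justify the looser level in view of the interim EBV results already reported.

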# 9. Data Analysis and Statistical Considerations

## 9.1 Study Design Considerations

This is a prospective, multi-center, controlled, open-label, randomized (1:1) phase Ⅳ study of comparison of different dosages ATG for GVHD prophylaxis (7.5 mg/kg vs. 10.0 mg/kg) in patients receiving haplo-HSCT. The primary Endpoint was incidence of EBV DNAemia within 1 year post-transplantation, and the study is designed to determine if 7.5 mg/kg ATG is superior to 10.0 mg/kg in the study population with respect to EBV DNAemia.

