### 9.2.1 Analysis of efficacy

For each numeric variable, the normality of distribution will be preliminarily assessed by the Kolmogorov-Smirnov test. Summary statistics, including proportions, mean, medians, and ranges, were used to describe the patient characteristics, pre-transplantation variables, adverse events, and immune recovery. The χ2 test and Mann-Whitney U test were used for categorical variables and continuous variables, respectively.

Time to acute GVHD, relapse, OS, and DFS were measured from the date of HSCT (d 0). OS and DFS were estimated using the Kaplan-Meier method. Considering the competing risks of death, cumulative incidence curves in a competing risks setting were used to calculate probabilities of aGVHD, cGVHD, viral infections (EBV- and CMV- emia as well as associated diseases) and relapse. The Cox proportional hazards model will be used to evaluate the associations of patient and transplant characteristics with outcomes in multivariate analysis. The risk factors for EBV and CMV infections include age and gender of patients; conditioning; EBV serostatus in patients and donors; CMV serostatus in patients and donors; ATG dose. The risk factors for aGVHD and cGVHD include age and gender of patients; conditioning; HLA disparity; age and gender of donors and ATG dose. The risk factors for survival and relapse include age and gender of patients; disease category; disease status; ATG dose.

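### The stated error and power rest on an unresolved choice of chi-square or Fisher on crude proportions, which does not match the competing-risk incidence of EBV DNAemia to be reported; under Fisher the 80% power is not met

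*Protocol*

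**What the plan says.** Protocol section 9.1 states the aim: "the study is designed to determine if 7.5 mg/kg ATG is superior to 10.0 mg/kg in the study population with respect to EBV DNAemia".

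Section 9.1.1 sizes the trial on two proportions: "Incidence of EBV DNAemia within 1 year post-transplantation in 7.5 mg group: 30"% and "Incidence of EBV DNAemia within 1 year post-transplantation in 10.0 mg group: 42"%. Item 4 sets a 5% one-tailed error under "no true underlying difference by Chi-square test" and offers Fisher's exact test as an alternative without choosing. Item 5 asks for 80% power and item 6 allows "5% percent of cases drop". The result is 412 patients, 206 per group.

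Section 9.2.1 takes a different route for the same endpoint. With death as a competing risk, "cumulative incidence curves in a competing risks setting were used to calculate probabilities of aGVHD, cGVHD, viral infections", and EBV DNAemia is among these infections. No test for comparing the curves is given. The section adds: "The Cox proportional hazards model will be used to evaluate the associations of patient and transplant characteristics with outcomes in multivariate analysis". Its factor list for EBV and CMV infection includes ATG dose. Chi-square appears there only as a general method for categorical variables.

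Section 9.2.2 makes all P values two-sided at 0.05, whereas item 4 of section 9.1.1 is one-tailed.

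**The concern.** The error and power promised in section 9.1.1 belong to a test of crude proportions. The incidence that section 9.2.1 will report is a competing-risk estimate.

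A crude test cannot use partial follow-up. A patient lost before 1 year must be either called EBV-free or dropped, and the protocol does not say which. The p-value and the reported incidence can therefore rest on different denominators. Within item 4 itself, Fisher is more conservative than chi-square, so the stated power cannot hold for both.

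The setting makes an open choice harder to defend. The trial is open-label, and the primary endpoint was changed after results by arm on the first 210 patients had been seen. A superiority claim close to the threshold would invite the question of when the deciding test was chosen.

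**Working it through.** **Inputs (section 9.1.1).** Control 0.42, experimental 0.30, one-sided 5%, 80% power, 1:1 allocation, 5% drop, 206 per arm.

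**1. Reproduce the plan's figure.** With unpooled variance:

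n = (1.645 + 0.842)² × (0.42×0.58 + 0.30×0.70) / 0.12² = 6.183 × 0.4536 / 0.0144 = 194.8, so 195 per arm.

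195 / 0.95 = 205.3, so 206 per arm and 412 in total. This matches. The sample size is that of a one-sided comparison of crude proportions.

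**2. Power of the two tests in item 4.** Computed by enumerating all binomial outcomes. After the drop, 206 × 0.95 = 195.7, taken as 195.

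| Per arm | Chi-square, one-sided 5% | Fisher, one-sided 5% |
| --- | --- | --- |
| 206 | 81.6% | 78.8% |
| 195 | 80.0% | 76.9% |

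Fisher misses 80% even with nobody lost; it would need about 216 evaluable patients per arm.

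**3. A result on which the two tests differ.** Take 87/206 against 70/206. The pooled rate is 157/412 = 0.381, the difference is 17/206 = 0.0825, and the standard error is √(0.381 × 0.619 × 2/206) = 0.0479. So z = 1.72 and one-sided p = 0.042 by chi-square. Fisher gives 0.052.

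**4. Crude test against competing-risk test.** Simulation, 206 per arm, 4,000 trials per scenario. The documents give no rate of death without EBV, so 10% and 15% in both arms were assumed, with 5% and 10% lost early.
- At 42% vs 30%, one-sided 5%: chi-square power is about 81% and Gray-type power about 80–81%.
- At 36% in both arms: each rejects in about 5% of trials.
- Under 42% vs 30%, the two disagree in about 3–4% of trials.

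**5. Cox.** If nobody died first, the hazard ratio would be ln(0.70)/ln(0.58) = 0.655. With 0.36 × 412 = 148 expected events, power is 82.5%, again close to chi-square. Cox departs when deaths without EBV differ between arms, because it compares the rate of EBV among patients still alive and EBV-free, not the 1-year incidence. Assume 20% vs 10% such deaths, in either direction, with 5% lost:
- Equal 36% EBV incidence: Cox rejects in about 8% of trials if control deaths are higher and about 3.5% if they are lower. Chi-square rejects in about 5%.
- 42% vs 30%: Cox power is about 87% or 74%, against about 81–82% for chi-square.

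**6. Sidedness.** Under the two-sided 0.05 of section 9.2.2, chi-square power is about 72% with 206 per arm and about 70% with 195. This is a loss of about 10 points, larger than the difference between the tests.

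**The case against.** **The methods have different purposes.** Sizing on two proportions while reporting a competing-risk curve is common. The cumulative incidence sentence in section 9.2.1 concerns estimation, and Cox is presented as a multivariate risk-factor analysis in which ATG dose is one item. Neither is offered as the superiority test. This stands: the protocol does not declare three rival primary analyses.

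**The SAP may settle it.** Section 9.2 defers to a prespecified statistical analysis plan, which is not at hand and may name the test. That also stands, and silence on the test would not be a finding by itself. What remains is in the protocol's own text: item 4 attaches one power figure to two tests that cannot share it, and the test it sizes does not match the estimator it prescribes.

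**Gray's test is not the only answer.** Naming chi-square with a fixed denominator would also remove the ambiguity. Gray's test is preferred because it matches the incidence the protocol says it will calculate.

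**A stronger reading that fails.** A reader might infer that the interim rates of 27.1% and 45.2% among the first 210 patients must be cumulative-incidence estimates, so that planning and testing use different methods. They need not be: 26/96 = 27.1% and 47/104 = 45.2% are simple proportions on 200 evaluable patients. That is 10/210 = 4.8% missing, close to the plan's 5%. The planning rates are also 30% and 42%, not the interim values.

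**Conclusion.** The point holds, at moderate weight. Item 4 of section 9.1.1 leaves the decision test open between two tests, and the stated 80% power is true of only one: 81.6% vs 78.8% at 206 per arm, and 80.0% vs 76.9% at 195. The test used for sizing also does not correspond to the incidence section 9.2.1 will report.

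A reader might go further and say that the trial's verdict generally turns on the method, or that choosing among methods would inflate the error substantially. The documents do not support that. Chi-square and a Gray-type test have nearly equal error and power and part in about 3–4% of simulated trials, so only borderline results are exposed. Larger error figures would require counting denominators that the protocol does not list.

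Cox can depart further, with about 4–8% rejection under equal EBV incidence, but only under the assumed 20% vs 10% imbalance in deaths without EBV. All simulation figures rest on assumed death and loss rates. The power figures for chi-square and Fisher need only the plan's own inputs.

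The sample size is not invalidated at one-sided 5%. It does not give 80% power if the two-sided rule of section 9.2.2 governs.

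**What to change.** In section 9.1.1, item 4, and section 9.2.1, name one decision analysis for EBV DNAemia within 1 year. Preferably:
- Gray's test over the first year, with death without EBV DNAemia as the competing event.
- Patients lost to follow-up censored at their last EBV-DNA test.
- The difference in 1-year cumulative incidence, with its confidence interval, as the reported effect. State that the test decides, since a whole-curve test and a 1-year difference can disagree at the margin.

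Remove Fisher as a decision test, keep chi-square only as the sizing approximation, and label the Cox model supportive.

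Settle sidedness in the same edit. If the test is one-sided at 5%, 412 patients give about 80% power and the matching interval is 90%. If the two-sided 0.05 of section 9.2.2 governs, use a 95% interval and restate the power as about 70–72%.

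The cost is a few sentences of protocol wording, with no extra data. Moving from chi-square to Gray's test leaves power nearly unchanged. The sponsor gives up the freedom to choose the method later and, if the test is two-sided, must acknowledge the lower power.

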### 9.1.2 Primary Efficacy Endpoint

The primary efficacy endpoint was incidence of EBV DNAemia post-transplantation

### 9.1.3 Secondary Efficacy Endpoints

The incidence of grade II to IV and grade III to IV aGVHD within 100 days post-transplantation; hematopoietic engraftment; cGVHD; EBV-associated diseases; CMV infections (CMV DNAemia and associated diseases); relapse; non-relapse mortality (NRM); OS; DFS and tolerance.

## 9.2 Data Analysis Considerations

All collected data will be checked by two physicians for completeness and plausibility, and data analysis will be conducted according to the prespecified statistical analysis plan.

Descriptive summaries for continuous data will include the mean, standard deviation, median, minimum, and maximum. Descriptive summaries of discrete data will include the frequency and percentage of each category, as well as overall frequency and percentage totals.

### 9.2.1 Analysis of efficacy

For each numeric variable, the normality of distribution will be preliminarily assessed by the Kolmogorov-Smirnov test. Summary statistics, including proportions, mean, medians, and ranges, were used to describe the patient characteristics, pre-transplantation variables, adverse events, and immune recovery. The χ2 test and Mann-Whitney U test were used for categorical variables and continuous variables, respectively.

Time to acute GVHD, relapse, OS, and DFS were measured from the date of HSCT (d 0). OS and DFS were estimated using the Kaplan-Meier method. Considering the competing risks of death, cumulative incidence curves in a competing risks setting were used to calculate probabilities of aGVHD, cGVHD, viral infections (EBV- and CMV- emia as well as associated diseases) and relapse. The Cox proportional hazards model will be used to evaluate the associations of patient and transplant characteristics with outcomes in multivariate analysis. The risk factors for EBV and CMV infections include age and gender of patients; conditioning; EBV serostatus in patients and donors; CMV serostatus in patients and donors; ATG dose. The risk factors for aGVHD and cGVHD include age and gender of patients; conditioning; HLA disparity; age and gender of donors and ATG dose. The risk factors for survival and relapse include age and gender of patients; disease category; disease status; ATG dose.

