# 3. Study Design

This is a prospective, multi-center, controlled, open-label, randomized (1:1) phase Ⅳ study of comparison of different dosages ATG for GVHD prophylaxis. (7.5 mg/kg vs. 10.0 mg/kg) in patients receiving haplo-HSCT

Screening:

The subjects or their legally acceptable representative will provide written informed consent. EBV and CMV antibody will be performed in all the haplo-HSCT recipients and donors before transplantation. EBV and CMV-DNA was tested in all the recipients and donors.

Treatment:

Based on their assignment, subjects will receive 7.5 mg ATG (2.5mg/kg/day from days -3 to -1 before transplantation) or 10.0 mg ATG (2.5mg/kg/day from days -4 to -1 before transplantation).

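### The only test tied to alpha and power for EBV DNAemia is unadjusted, and the protocol's own baseline predictors enter only a non-primary Cox model: a valid choice that may give up a little efficiency

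*Protocol*

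**What the plan says.** The sample-size assumptions in Protocol section 9.1.1 include "Incidence of EBV DNAemia within 1 year post-transplantation in 7.5 mg group: 30" percent, "Incidence of EBV DNAemia within 1 year post-transplantation in 10.0 mg group: 42" percent, "a 1:1 randomization scheme" and "a 5% 1-tailed risk of erroneously claiming a difference". Item 4 ties that risk to the test: "no true underlying difference by Chi-square test or Fisher" (the exact test). No covariates are mentioned. With 80% power and 5% dropout, the stated total is 412, or 206 per group.

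Section 9.2.1 assigns the chi-square test to categorical variables in general. It estimates viral infections by cumulative incidence with death competing, and names no between-arm test for those curves. It then describes a multivariable Cox model and its candidate factors: "The risk factors for EBV and CMV infections include age and gender of patients; conditioning; EBV serostatus in patients and donors". The list continues with CMV serostatus of patients and donors, and with ATG dose.

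The serological factors are already collected. Section 3 says that "EBV and CMV antibody will be performed in all the haplo-HSCT recipients and donors before transplantation".

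Sections 6.2 and 9.1 make the primary question the incidence of EBV DNAemia within 1 year, tested for superiority of the 7.5 mg/kg arm.

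**The concern.** The protocol names the baseline factors it expects to be related to EBV infection and measures serostatus in every recipient and donor before transplantation. It then links alpha and power to a comparison that uses none of them. Adjusting a randomised comparison for baseline predictors of the outcome usually improves precision and accounts for whatever imbalance occurs in the realised sample, without more patients.

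The Cox model does not bring this gain to the decision. Its dose effect is a hazard ratio, whereas the endpoint is a 1-year proportion. Because section 9.2.1 treats death as a competing event, that hazard ratio does not translate directly into a difference in 1-year incidence. Two dose effects on one endpoint would be produced on different scales, and only the unadjusted one is connected to the stated error rate. At stake are a few points of power at most, and clarity about which result decides.

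**Working it through.** **Inputs from section 9.1.1:** rates 0.42 and 0.30 (difference 0.12), 1:1 allocation, one-sided 5%, power 80%, dropout 5%, 206 per arm. **From section 9.2.2:** P values are two-sided at 0.05. **Not in the documents:** the share of outcome variance explained by the listed factors (R²), taken here as an assumed range of 2% to 10%.

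**Step 1: reproduce the plan's figure.** With unpooled variance, n = (1.645 + 0.842)² × (0.42×0.58 + 0.30×0.70) / 0.12² = 6.18 × 0.4536 / 0.0144, which rounds up to 195 per arm. Allowing for dropout, 195 / 0.95 rounds up to 206 per arm, or 412 in total. The stated figure is matched exactly by an unadjusted one-sided test.

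**Step 2: power without adjustment.** Evaluable patients: 206 × 0.95 ≈ 196 per arm. Mean rate 0.36.
- SE under the null = √(2 × 0.36 × 0.64 / 196) = 0.0485.
- SE under the alternative = √(0.4536 / 196) = 0.0481.
- One-sided 5%: Φ((0.12 − 1.645 × 0.0485) / 0.0481) = 79.9%.
- Two-sided 5%: Φ((0.12 − 1.960 × 0.0485) / 0.0481) = 69.8%.

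**Step 3: power with adjustment.** Multiply both variances by (1 − R²), which is the same as replacing 196 by 196 / (1 − R²). The last column is 412 × R², the number of patients that the gain is worth at equal power.

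| Assumed R² | One-sided 5% | Two-sided 5% | Worth, of 412 patients |
| --- | --- | --- | --- |
| 0 | 79.9% | 69.8% | 0 |
| 2% | 80.6% | 70.7% | about 8 |
| 5% | 81.6% | 72.0% | about 21 |
| 10% | 83.4% | 74.3% | about 41 |

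The gain is 0.7 to 3.6 points one-sided and 0.9 to 4.5 points two-sided.

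**Step 4: check by simulation.** In 4,000 simulated trials per setting with 196 per arm, an unadjusted z-test was compared with logistic regression adjusted for one prognostic score. One-sided power, unadjusted against adjusted, was 79.9% and 80.1% at R² of about 2%, 80.0% and 81.3% at about 5.5%, and 79.8% and 83.0% at about 10%. The direction agrees with step 3, and the gains are slightly smaller.

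**Step 5: can the data carry the model?** Expected events are 196 × 0.30 + 196 × 0.42 = 58.8 + 82.3, about 141 among 392 evaluable patients. That is enough for the handful of factors listed.

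**The case against.** The strongest reply is that nothing here is an error. An unadjusted comparison in a 1:1 randomised trial is valid, the plan's 80% power is met under its own one-sided assumption, and covariate adjustment is often left to the statistical analysis plan, which section 9.2 cites and which is not at hand. The deciding test is also not firmly fixed. Item 4 of section 9.1.1 is a sample-size assumption, and the chi-square sentence in section 9.2.1 is general. These points stand, and they limit the finding to an optional gain. They do not remove it, because the protocol itself links the primary error rate to an unadjusted test and places its named predictors elsewhere.

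Three stronger readings are tempting, and the documents do not support them.

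- A reader might infer that the protocol plans no adjusted dose effect. It does: ATG dose is in the same Cox list.
- A reader might infer that the primary P value is exposed to chance imbalance. Randomisation and the test's error rate already allow for it on average. Without adjustment there is no correction for the imbalance that actually occurs, but there is no bias and no inflation of type I error.
- A reader might infer that adjustment would settle the conflict between the one-sided 5% of section 9.1.1 and the two-sided 5% of section 9.2.2. That conflict moves power from about 80% to about 70%. Even at an R² of 20%, twice the top of the range assumed here, two-sided power reaches only 79.2%.

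It is also fair to object that arm-level EBV results for 210 patients have been seen (27.1% against 45.2%), so any new analysis choice comes after a comparative look. That is a real downside, and the conditions placed on the change must answer it.

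**Conclusion.** The point holds as a modest, optional improvement. The protocol's only test linked to alpha and power for the primary endpoint leaves out the baseline factors that the protocol itself names. The adjusted dose estimate it does plan is a hazard ratio without primary status. The loss is efficiency, not validity.

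Its size rests entirely on an assumed R², because the documents say nothing about how strongly the factors predict. It is about 1 to 5 points of power at an R² of 2% to 10%, taking both choices of sidedness together. It is near zero if serostatus hardly varies among these patients or the factors predict weakly.

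**What to change.** In section 9.1.1 item 4 and section 9.2.1, name one primary comparison of 1-year EBV DNAemia by randomised arm, adjusted for pre-randomisation factors already listed in section 9.2.1: patient age and gender, and recipient and donor EBV and CMV serostatus. Include conditioning only if the regimen is set before randomisation. The protocol does not say whether it is, and the trial is open-label. State the categories and a rule for collapsing sparse ones.

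Use a single method fixed in advance that treats death as a competing event, so that the choice does not depend on the censoring observed. Regression on 1-year cumulative-incidence pseudo-values would serve, reported as a risk difference with a 95% confidence interval. Keep the unadjusted test as supportive and the Cox model as the risk-factor analysis. The sample size need not change.

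The cost is a wording change and a few lines of analysis code, with no new data or patients. Because it is a further analysis change after the arm-level look at 210 patients, it must be dated, confined to the listed factors, and fixed before any further arm-level data are seen. The conflict between one-sided and two-sided testing needs its own correction.
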